### Data Analysis

#### Analysis of SN Data

The primary outcomes, SV and DV, were analyzed as binary variables, constructed as lifetime and past 12-month indicators of experiencing that form of violence. Secondary outcomes, most of which are assessed as scales, were continuous variables based on mean scores across included items.

We used baseline SN data to understand the clustering of social norms and behaviors within this study’s population (aim 1). To do this, we have described the network characteristics of the sample and assessed how SV social norms and experiences of SV and DV are associated among nominator-nominee dyads. We used dyadic observations from the baseline data for each pair of socially connected youth (dyad; eg, ego and alter 1, and alter 1 and alter 2) to restructure the dataset. We calculated whether having a peer who adheres to a particular norm or behavior was predictive of corresponding responses from paired versus nonpaired individuals. This was done using logistic regression analysis (outcome: yes or no) using a generalized estimating equation to account for correlation among dyads. We assessed for effect modification of these relationships based on the types of relationships (eg, school or other peer, or family), the mode of communication, gender concordance, and racial concordance. This analysis provided us with pertinent insight into what norms, attitudes, and behaviors were clustered among socially connected people, and across what relationships, creating a map for understanding opportunities for SN-based intervention. This manuscript is in preparation for publication.

Our primary analysis for main effects (aim 2) will be designed to assess the effects of the intervention on the prevalence of past 12-month SV and DV (sexual assault, online and in-person SH, DV, and LGBTQ+-specific SV) at 24-month follow-up. Our secondary analysis for secondary outcomes (aim 2) will be designed to assess the effect of the intervention on SV attitudes, behavioral intentions to intervene to prevent SV, reported intervention behavior, perceived behavioral self-efficacy to prevent SV, social norms of the acceptability of SV, and community connection and cohesion. First, we will conduct descriptive analyses to explore differences at baseline between the intervention and control groups and factors associated with loss-to-follow-up to understand how these factors may contribute to possible bias in our results. Then, we will assess change over time and by group via adjusted hierarchical difference-in-differences regression analyses to account for unmeasured and measured baseline differences between intervention and control groups, controlling for sampling level (ego, alter 1, and alter 2), accounting for clustering by community, and confounders identified using a dialectical acyclic graph [54]. The difference-in-differences approach does not rely on the strength of the match between intervention and control groups, but rather accounts for baseline differences, offsetting the impact of the three poor intervention-control matches that exist in the sample. Furthermore, we will adjust for factors associated with treatment group assignment to further account for baseline differences. In sensitivity analyses, we will use modern difference-in-differences approaches, such as group weighting approaches proposed by Callaway and Sant’Anna [55], to account for recent developments in understanding potential violations of parallel trends. Subanalyses will be conducted to assess for interaction at each sampling level (ego, alter 1, and alter 2), by gender, LGBTQ+ identity, race or ethnicity, and triangulating with process data. Process data effect modification analyses will assess whether implementation quality, program dosage, and characteristics of program sites modify the observed effect of the intervention on primary and secondary outcomes. Sensitivity analyses will be conducted to assess the variability of effects related to potential violations of the parallel trend assumption, low response rates if they unexpectedly occur, and bias due to potential differences in intervention and control response rates. In addition to the intention-to-treat analysis described above, we will conduct an as-treated analysis based on individual-level dosage estimates from process data. Finally, we will conduct a sensitivity analysis to account for loss-to-follow-up using inverse probability of censoring weighting [56] based on baseline data, should significant baseline differences exist between those lost and those retained. All analyses will be complete case analyses.

Additionally, using SN data, we will test for social diffusion of intervention via SNs (aim 2) via multiple methods. To test the effect of social influence on attitudes, norms, and behaviors, we will use the dyadic dataset of nominator-nominee pairs to test for the effect of social contacts’ attitudes, norms, or behaviors at 24-month follow-up, controlling for both of their own attitudes, norms, or behaviors at baseline and demographics related to these outcomes at baseline. We will explore a variety of model specifications during our analyses and conduct diverse robustness checks given the quasi-experimental design. As we will know whether network nominations are reciprocal (ie, if ego A nominated first tier alter A, did first tier alter A nominate ego A in return?), we can evaluate the possibility of omitted variables or confounding events explaining the associations by examining how the type or direction of the social relationship between ego and alter affects the association between ego and alter (using a “network directionality” test) [57]. Additionally, we will also conduct a sensitivity analysis in which we estimate the bias in the association between ego and alter that might be caused by an omitted variable that is correlated with the prevalence of the outcome variable in both ego and alter [58]. This class of omitted variables includes those that explain friendship formation based on a trait (homophily) and confounding environmental factors that may affect the ego and alter relationships.

Network effects likely will not be uniform across subgroups. For this reason, we will conduct a series of subgroup analyses, looking at potential moderators of potential network effects based on what we learn about the SN characteristics from baseline data. By running a series of interaction models on our main effect analyses, we will consider whether diffusion differs depending on gender, LGBTQ+ identity, the strength of the connection, and other potential moderators such as age, ethnicity, experiences of violence, and program exposure.

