##### SN Data Statistical Power

We powered the matched cluster evaluation trial to have .80 power to detect a reduction in 12-month incident SV (the primary outcome) at α<.05. We estimated we would have a follow-up sample of 791 youth study participants (baseline sample: n=953, 791/953, estimated 85% retention at follow-up) from the SN data collection across 22 study sites (11 C2H and 11 control; estimated 36 youth per cluster). We assumed that the average baseline 12-month incidence of the primary outcome would remain constant for the control group at follow-up (107/395, 27% past 12 months SV). The minimal detectable effect would therefore be a 32% (.27 × .32) reduction in SV (71/396, 18% for 12 months incidence at follow-up). Reducing SV by 32% is feasible, given that a previous rigorous evaluation of the shifting boundaries SV prevention model detected a 43% and 50% reduction in SV [40,41]. Furthermore, 37.5% (297/791) of the sample identified as a sexual and/or gender minority (ie, LGBTQ+), among whom 42.4% (126/297) report SV. Estimating the minimal detectable effect for this subsample (297/791 of follow-up participants, 37.5%, 14 LGBTQ+ youth per site), and a 42.5% baseline incidence for LGBTQ+ controls, this study was also powered to detect a 33.5% (0.335 × 0.425=0.14; 0.425-0.14=28% for 12 months incidence at follow-up, 83/297) reduction in LGBTQ+ SV experiences.

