#### LGBTQ+-Targeted Forms of SV and DV

A measure to assess experiences with forms of SV and DV targeting LGBTQ+ youth was developed by the research team. Survey participants who selected an LGBTQ+ sexual and/or gender identity received a module (via skip patterns) that contained items assessing forms of violence targeting LGBTQ+ youth, and those selecting an expansive gender identity (ie, any gender except cisgender boy or girl) received an additional set of items assessing forms of violence targeting gender expansive youth. Items included in these assessments were adapted from two existing scales developed for adults: the Identity Abuse Scale [43] and the Transgender-Specific Intimate Partner Violence Scale [44]. They were reviewed by both practice and research experts on this topic and pilot tested with LGBTQ+ youth.

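### The primary outcome is stated inconsistently, so the 5% error rate and 80% power are secured only if 12-month sexual violence alone decides success

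*Protocol article*

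**What the plan says.** - **Abstract (Methods) and Introduction (last paragraph).** SV and DV are both primary, and the Introduction says this was set in advance. The Abstract uses a 12-month window and names four forms: sexual assault, in-person harassment, online harassment and DV.
- **SN Data Statistical Power.** One outcome is powered, in the singular: "a reduction in 12-month incident SV (the primary outcome) at α<.05". The sample is a "follow-up sample of 791 youth study participants" and the control rate is "107/395, 27% past 12 months SV". A second statement covers SV among LGBTQ+ youth. DV has no power statement.
- **LGBTQ+-Targeted Forms of SV and DV**, placed under Primary Outcomes. These items come from a separate module: "Survey participants who selected an LGBTQ+ sexual and/or gender identity received a module (via skip patterns".
- **Analysis of SN Data, first paragraph.** "The primary outcomes, SV and DV, were analyzed as binary variables, constructed as lifetime and past 12-month indicators of experiencing that form of violence".
- **Analysis of SN Data, main effects.** The primary analysis concerns past-12-month SV and DV, followed by a bracket: "sexual assault, online and in-person SH, DV, and LGBTQ+-specific SV".
- **Hypothesized Main Results.** A reduction in past-12-month SV and DV, with the Abstract's four forms and no LGBTQ+-specific outcome.
- **Analyses of California Healthy Kids Survey Data.** Primary and secondary outcomes are estimated again in the school survey (CHKS).

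**The concern.** These sections do not describe the same primary outcome. It is one outcome in the power section, two in the Introduction, and two or five in the main-effects paragraph, depending on how the bracket is read. LGBTQ+-specific SV is in the primary analysis but not in the Abstract or the hypothesis. It also has a different denominator, about 37.5% of the expected sample (297/791). The power statement for LGBTQ+ youth concerns their SV experience and not the forms measured by the separate module.

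The lifetime wording is a further conflict. Among the same youth followed for 24 months, a consistently reported lifetime indicator can only stay the same or rise. Its follow-up value also includes events from before baseline. The groups could differ in how much it rises, but it cannot show the hypothesised reduction.

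The study is not randomised, and follow-up closed in November 2025. If the deciding outcome is still open when results are seen, the choice can follow the result, and the 0.05 stated for one outcome no longer describes the claim.

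**Working it through.** **1. The sections side by side**

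| Section | Outcomes named | Window |
|---|---|---|
| Abstract | SV and DV; four forms | 12 months |
| Introduction | SV and DV | not given |
| SN Data Statistical Power | SV only | 12 months |
| Experiences of SV and DV | forms of harassment, assault and DV | both measured |
| Analysis of SN Data, first paragraph | SV and DV | lifetime and 12 months |
| Analysis of SN Data, main effects | SV and DV; five forms | 12 months |
| Hypothesized Main Results | SV and DV; four forms | 12 months |

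Every section that states the intended effect uses 12 months. The number of outcomes is not settled.

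**2. The plan's own figure**

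Inputs from SN Data Statistical Power: control rate p1 = 0.27; 32% relative reduction, so p2 = 0.27 × 0.68 = 0.1836; alpha 0.05 (two-sided assumed, as the section does not say); power 0.80; 791 youth, or 395.5 per arm.

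Formula: n = [z(α/2)·√(2·p̄·q̄) + z(β)·√(p1q1 + p2q2)]² / (p1 − p2)²

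- p̄ = 0.2268, so √(2 × 0.2268 × 0.7732) = 0.5922.
- √(0.1971 + 0.1499) = 0.5891.
- n = (1.960 × 0.5922 + 0.8416 × 0.5891)² / 0.0864² = 368 per arm.
- With continuity correction: 391 per arm, 782 in total, against 791 stated (1.1% apart).

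The figure reproduces as one test of one outcome at the full 0.05, with no share of alpha held back for DV or any single form.

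**3. Error rate if more than one outcome can carry the claim**

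With k independent tests at 0.05, any one counting: 1 − 0.95^k. Correlated cases come from simulating equally correlated z statistics (400,000 draws). The correlations are assumptions, because the article gives none.

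| Tests | r = 0 | r = 0.5 | r = 0.7 | r = 0.9 |
|---|---|---|---|---|
| SV and DV (2) | 9.8% | 9.1% | 8.4% | 7.0% |
| Five forms | 22.6% | 18.3% | 14.8% | 10.2% |

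These count false positives in either direction. Counting only those that favour the program, where a single two-sided 0.05 test has 2.5%, two tests give 5.0% to 3.5% and five give 11.8% to 5.2% (r = 0 to 0.9).

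**4. Power if alpha is shared**

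Power = Φ{[(p1 − p2)·√n − z(α/2) × 0.5922] / 0.5891}

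- Alpha 0.025 (z = 2.241), n = 368: (1.657 − 1.327)/0.5891 = 0.560, power 71%.
- Alpha 0.025, n = 395.5: (1.718 − 1.327)/0.5891 = 0.664, power 75%.
- Alpha 0.01 (five-way Bonferroni, z = 2.576): 59% and 63%.

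Here n = 368 is the size that gives exactly 80% at 0.05, and n = 395.5 makes no allowance for clustering. The 746 youth who responded are 373 per arm if split equally, which lies between the two.

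**The case against.** The strongest reply is that the article is a condensed text. It says an analysis plan is registered, and multiplicity handling commonly sits there. That stands: the absence of an alpha-sharing rule is no finding in itself, and nothing here shows that the 5% rate is breached. But the point does not rest on a missing rule. A rule shares alpha across a defined set, and this article defines the set differently from section to section.

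Four stronger readings are tempting, and the article does not support them:

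- **That the powered outcome is missing from the primary analysis.** It is not. The main-effects sentence names past-12-month SV and DV before the bracket, and the bracket may simply list what they comprise. The article never says that each form is tested alone or that any one suffices.
- **That lifetime versions double the primary tests to ten.** Ten independent tests would give 40%, but the main-effects paragraph and the hypothesis are limited to 12 months. The lifetime phrase describes how variables were built, just before the baseline network analysis.
- **That the individual forms have some particular low power.** The article gives no control rates for them, so no single figure can be defended.
- **That CHKS adds further primary tests.** It has its own power statement, analysis section and level of inference, and none of the error rates above include it. The article does not say, however, which source carries the main claim.

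**Conclusion.** The inconsistency is real and can be read directly from the article. The stated 5% error rate and 80% power go together only if past-12-month SV alone decides success. Otherwise the size is conditional: up to about 10% if SV and DV are each tested at 0.05 and either counts, and about 10% to 23% if the five forms are tested separately and any one counts. This rests on two-sided tests, no adjustment and assumed correlations from 0.9 to 0. A reader might infer that the trial's error rate is already lost; the article supports only that it is not secured as written. Nor does the inconsistency show that DV should lose its primary status, since the Introduction makes it primary in advance. This should be corrected before the main-effects analysis, but it does not undermine the design.

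**What to change.** Before the 2026 main-effects analysis, and checked against the registered outcomes:

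1. State that the primary effect uses past-12-month indicators in the SN sample. Use lifetime indicators only for description or as covariates.
2. Choose one of two routes. Either name any past-12-month SV, the powered outcome, as the deciding outcome; or keep SV and DV as co-primary with a stated alpha-sharing rule such as Holm, and restate the power.
3. Make the individual forms secondary, with LGBTQ+-specific SV analysed among LGBTQ+ youth.
4. Say whether the CHKS analysis is supportive.

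The work is in the wording. With a single deciding outcome, the stated sample size and power calculation is unchanged. With two co-primaries, power for the 27% to 18.4% effect is about 71% to 75% at alpha 0.025, and power for DV needs its own control rate. The cost is that a lone positive component can no longer be called a primary result. Any departure from the registered outcomes must be reported as made after data collection and before analysis.

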#### SN Primary Data Collection

##### Youth Recruitment

Youth program participants ages 14‐24 years were recruited to this study from each C2H site and the matched control site within 6 months of one another (henceforth, “egos”). Ego recruitment was initiated at a C2H site as soon as the site had recruited and established a youth team to begin a new cycle of C2H implementation, between October 2021 and May 2023. Due to major disruptions caused by the COVID-19 pandemic, C2H implementation began at different time points across sites; 7 sites started in the fall of 2021 and 4 sites started in the fall or winter of 2022‐2023.

To recruit youth, the cofirst author attended a regular C2H/4-H meeting (in-person or virtual), shared this study’s purpose, the SN recruitment process, the risks and benefits of participating, compensation, and, after all questions were answered, invited youth to participate in this study. Those who were interested in participating were sent a personalized link using a provided phone number or email address. Research staff provided tablet devices, device chargers, a Wi-Fi hotspot, and snacks to participants as needed. After this initial meeting, as new youth were recruited to the C2H/4-H groups, research staff continued recruitment as needed, providing virtual or in-person survey orientations as needed to invite all C2H/4-H members to participate and maximize ego recruitment.

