Youth accessed the survey via a Qualtrics link, which began with an electronic informed assent or consent form, proceeded to eligibility screening, and concluded with the full survey instrument. Eligibility criteria included being between the ages of 14 and 24 years, currently living in California, being a current participant in a C2H or 4-H group (or for nominated alters, being nominated by a current participant), and providing informed consent or assent. Youth who declined to participate or were not eligible to participate were offered an alternative online activity to do while others were taking the survey to conceal participation. The survey took approximately 40 minutes to complete. At the end of the survey, youth were asked to provide their contact information so that they could receive online incentives and be recontacted for retention check-ins and for the 24-month follow-up survey. Participants received a US $20 online gift card within 24 hours of completing the survey. All survey participants were provided with an online list of resources (eg, SV, sexual harassment and DV advocacy, LGBTQ+ support, and mental health services).

To gather data on SN members (henceforth, “alters”) of the egos, the survey included SN name generator questions to prompt participants to identify up to 10 peers from their SN (ie, “alter 1 s”). Refined via pilot testing, the name generator question prompt was “of the people in your life who live, go to school, or work in or very close to [geographic location of the community site] and are between the ages of 14 and 24…” and the specific name generator questions were “Who do you consider a close friend (including any dating/romantic partners you have)?” “Who are the people that you participate in activities with and who you also consider a friend (activities could include things like sports, jobs, online or in-person meetings, after-school clubs, or other groups involving people around your age)?” and “Besides your close friends, who do you talk to about issues that are important to you?”

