Once a nominated peer accessed the survey link (on their own device, in a location or time of their choice), they completed the same assent or consent form as egos, followed by a modified eligibility screening that included confirmation of being between the ages of 14 and 24 years, being new to the survey (ie, not having taken it before), and knowing the person that nominated them. Additionally, when a nominated peer accessed the survey link, a US $10 incentive was sent to their ego nominator in acknowledgment of their time and effort to recruit their peer. Once screened, these peers became “alter 1s,” received the same survey, the same opportunity to nominate up to 10 peers (yielding potential “alter 2s”), and the same request for providing their contact information and their nominated peer’s contact information as the egos. Upon completion of a survey by an alter 1, the alter 1 received a US $20 gift card within 24 hours. Alter 2 recruitment and participation mirrored that of alter 1 s except they were not asked to nominate peers or provide peer contact information. Alter 2 s received a US $25 gift card for taking the survey, and alter 1, who nominated them, received US $10 when they accessed the survey link. Alter 1 and alter 2 surveys included an embedded video created by the YRAB explaining this study and the risks and benefits of participation, providing similar information as is provided during the ego survey orientation.

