##### Follow-Up SN Data Collection

Implementation of the four C2H phases required a minimum of 12 months. Follow-up data were collected 24-months postbaseline. Follow-up surveys were self-administered via an online link by the youth. We reached out to participants when 24 months had passed since their baseline participation via the provided contact information, updated via retention efforts, and reminded them weekly of the opportunity to participate in follow-up data collection to minimize loss to follow-up. Participants received a US $50 incentive for completing the follow-up survey. See Multimedia Appendix 2: Close to Home evaluation participant timeline.

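### Adjusting for sampling level as a main effect cannot remove an ego-only change in survey setting if the ego share differs by arm; adding sampling level × wave costs almost nothing

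*Protocol article*

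**What the plan says.** **Egos at baseline** (Protocol article, Youth Recruitment). Egos were approached at a regular C2H or 4-H meeting, held in person or virtually. Those interested "were sent a personalized link using a provided phone number or email address". At the session, "Research staff provided tablet devices, device chargers, a Wi-Fi hotspot, and snacks to participants as needed". Youth who declined or were ineligible "were offered an alternative online activity to do while others were taking the survey to conceal participation". For members who joined later, "research staff continued recruitment as needed, providing virtual or in-person survey orientations as needed".

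**Alters at baseline** (same section). They opened the survey "on their own device, in a location or time of their choice".

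**Everyone at follow-up** (Follow-Up SN Data Collection). "Follow-up surveys were self-administered via an online link by the youth".

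**Primary model** (Analysis of SN Data). An adjusted hierarchical difference-in-differences regression, "controlling for sampling level (ego, alter 1, and alter 2), accounting for clustering by community", plus confounders. All analyses are complete-case. Interaction by sampling level is planned as a subanalysis, and possible violations of parallel trends are left to sensitivity analyses.

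**The concern.** The primary outcomes are self-reported experiences of sexual and dating violence, for which the surroundings in which a youth answers may matter. The alternative activity that concealed who was taking part shows that the team saw a privacy issue in the session. It also implies that at least some egos answered while others were present. Alters did not, and at follow-up nobody is described as doing so. The setting may therefore have changed between waves for one sampling level only.

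Difference-in-differences removes what is constant over time and what changes equally in both arms. A change confined to egos enters each arm's trend in proportion to that arm's ego share. That share was not fixed by design: it depends on club size, on later joiners and on how many nominated peers took part. The mix of in-person and virtual sessions was not assigned either.

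Suppose egos report more freely at follow-up. If the C2H arm has the larger ego share, violence appears to rise there and a benefit is masked. If it has the smaller share, the same shift looks like a program effect.

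**Working it through.** **1. Yardstick from the plan** (SN Data Statistical Power). The planned effect is a 32% relative reduction from 27%: 0.27 × 0.32 = 0.0864, so 27% falls to about 18.4%, which the plan rounds to 18%. This is 8.6 to 9 points. It serves only to judge the size of a bias. No stated figure is disputed here.

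**2. Bias formula.** Let s_T and s_C be the ego shares in the C2H and control arms, and d the ego-only change in reported prevalence from baseline to follow-up. Assume no true effect and no change in alters.

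- Change in the C2H arm: s_T × d
- Change in the control arm: s_C × d
- Difference-in-differences: (s_T − s_C) × d

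**3. Why a main effect does not help.** With complete cases at two waves, each youth has the same sampling level at both. The sampling-level indicator is therefore constant over waves and unrelated to the arm × wave term once arm and wave are in the model. In a linear model it leaves the arm × wave coefficient unchanged. A sampling level × wave term takes up s × d in each arm and returns the coefficient to zero, provided d is the same in both arms.

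**4. Numbers.** The article gives neither the ego shares by arm nor d, so both are assumptions. Bias in percentage points, fitted to expected cell values:

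| Ego share, C2H vs control | d = 2 | d = 5 | d = 10 |
|---|---|---|---|
| 30% vs 30% | 0.0 | 0.0 | 0.0 |
| 35% vs 25% | 0.2 | 0.5 | 1.0 |
| 40% vs 20% | 0.4 | 1.0 | 2.0 |
| 45% vs 15% | 0.6 | 1.5 | 3.0 |

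Every entry is the same with no sampling-level term and with a main effect. Every entry is 0.0 with sampling level × wave.

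**5. Logistic version.** With 40% vs 20% egos and assumed baseline prevalences of 30% in egos and 27% in alters, the spurious odds ratio is about 1.02, 1.05 and 1.10 for d = 2, 5 and 10. The main effect leaves these essentially unchanged. With sampling level × wave the odds ratio is 1.00.

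**6. Where the interaction is not enough.** If d differs by arm, say 5 vs 2 points with 30% egos in both, the bias is 0.30 × (5 − 2) = 0.9 points and sampling level × wave leaves it in place. An unequal mix of in-person and virtual sessions could produce such a difference. If only in-person egos shift, by 3 to 10 points, and the in-person share differs by 20 to 40 points between arms, the estimate among egos is off by 0.20 × 3 = 0.6 to 0.40 × 10 = 4.0 points. With 30% egos in both arms, the pooled estimate would be off by 0.30 times that, about 0.2 to 1.2 points.

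**The case against.** A reader might infer that an ego-only change of setting by itself contaminates the estimate. The article does not support that. One ego procedure is described for both programs, and Informed Consent and Assent gives identical recruitment in the two arms as an aim. A shift shared by both arms, with equal ego shares, cancels exactly (first row of the table). No imbalance is reported.

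It would also be too strong to say that egos answered in a group at baseline and by link at follow-up. Baseline too was a self-completed personal link, so the survey mode did not change. Some sessions were virtual, later joiners were handled separately, and tablets were lent only where needed. No passage says that reporting was suppressed.

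Three further points are fair:

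- **Size.** The top of the range needs a 30-point imbalance in ego share and a 10-point shift. On a 27% outcome, that shift means 10/27, or about 37%, of ego reports missing at baseline.
- **Other planned analyses.** A contrast within egos cancels a common shift whatever the mix, and the parallel-trend sensitivity analyses address this class of problem. They may reveal it, but they do not change the pooled primary estimate.
- **Specification.** The article's phrase does not exclude an interaction with wave, and a fuller analysis plan may contain one. The point applies to the phrase read as a main effect, its ordinary sense.

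What stands is the algebra in step 3, and the fact that identical procedures do not guarantee identical sampling-level mixes.

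**Conclusion.** The point holds in conditional form. The text supports a change of setting confined to egos, at least for some of them, and a sampling-level main effect cannot absorb a change specific to one level. Bias follows only if the ego share, or the setting mix among egos, differs between arms and the setting affects reporting. The documents establish neither condition.

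From unequal ego shares, the bias runs from 0.2 to 3.0 points over the assumed grid. The middle case (40% vs 20% egos, 5-point shift) gives 1.0 point, about 12% of the 8.6-point planned effect. That would rarely overturn an effect of the planned size. It matters more for the modest effects that the authors say they expect. This is a worthwhile low-cost improvement to the primary model and not a flaw that invalidates it.

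**What to change.** 1. In the primary difference-in-differences model, state that sampling level (ego, alter 1, alter 2) enters both as a main effect and as sampling level × wave. If the full analysis plan already does this, no change is needed beyond saying so.
2. Report the sampling-level mix by arm in the analyzed sample.
3. If baseline setting (in-person or virtual session) was recorded for egos, report it by arm and add setting × wave among egos as a sensitivity analysis. The article does not say that it was recorded, and Process Data Collection does not list it. If it was not, state this as a limitation.

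Cost: items 1 and 2 need a sentence of wording before the main-effect analysis planned for summer to fall 2026. They use two degrees of freedom, with 746 youth followed up, and a variable already in the model. Item 3 depends on records that may not exist. Item 1 removes the bias only if the ego shift is common to both arms, which is why item 3 is worth attempting.
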